## Methods

### Trial design

This confirmatory study is designed as a multi-center, non-blinded, two-armed, parallel-group, randomized controlled trial over 6 months. This design is oriented towards two previous studies from the US and Finland [10, 11]. Participants will be randomly assigned to either an intervention group, who completes JOBS Program Germany right away or a waiting control group, who will not participate in JOBS Program Germany during the trial. The allocation ratio will be 1:1. Primary and secondary outcomes (see below) will be repeatedly assessed at three points in time: (1) immediately before the intervention (*t*_*0*_), (2) immediately after the intervention (*t*_*1*_), and (3) 6 months after the intervention has ended (*t*_*2*_; see: Fig. 1).

**Fig. 1 Fig1:**
[figure not shown]
Schedule of enrollment, interventions, and assessments

### Study setting

The JOBS Program Germany is embedded into the large-scale prevention program “Linking of Employment Promotion and Health Promotion in the Community Setting” in Germany. This is a joint program by the National Association of Statutory Health Insurance Funds, the health insurance companies, the Federal Employment Agency, Jobcenters, the Association of German Counties, and the Association of German Cities. The BZgA coordinates the joint, country-wide activities in approximately 230 locations. Interventions will be conducted in the community-settings of these locations. The data will be collected centralized by the Institute for Social Sciences and Communication (SOKO) on behalf of BZgA and in close coordination with the research team at the University of Kassel. Computer-assisted telephone interviews (CATI) will be conducted based on questionnaires developed by the research team at the University of Kassel. The data will be analyzed exclusively by the research team at the University of Kassel. The sample will comprise adult men and women who are unemployed according to the German Social Code, Book III, and who are willing to participate in the JOBS Program Germany voluntary.

### Intervention

The intervention is based on the JOBS Program that was developed by the Michigan Prevention Research Center [6, 7]. The JOBS Program Germany for the unemployed is conceptualized as a workshop that combines job application training with elements of social learning theory and self-efficacy [8, 9]. More specifically, participants discuss potential problems, difficulties, and setbacks during the job-search process while also developing coping strategies and the skills to overcome these challenges. Trainers provide emotional support by constantly giving positive feedback. In sum, the JOBS Program Germany centers around the following concepts (for a detailed description, see the respective JOBS Manual [5]):
Job-search skillsActive teaching/learning methodsInoculation against setbacksTrainer referent powerSocial support

Accompanied by a team of two trainers, the intervention group completes JOBS Program Germany in small groups of 8 to 15 unemployed people for 5 days in units of 5 h a day over a period of 1 week. Trainings will be completed in the community-settings at each of the participating locations.

Resembling the Finnish implementation of the JOBS Program [11], trainers will partly be recruited from unemployed jobseekers. In each trainer team, one unemployed person will be paired up with a professional trainer, usually an employee at the local Jobcenter, who has some experience in offering regular job application trainings. The training of the trainers is conceptualized in cooperation with the Finnish Institute of Occupational Health and follows a translated version of the original JOBS Program protocol.

### Waiting control group

While the JOBS Program Germany is free of charge for the participants, similar prevention and health promotion programs for the unemployed, according to paragraph 20 of the German Social Code, Book V, are usually associated with participant fees. Because there is no equivalent free-of-charge health promotion program for the unemployed, we have opted for a passive waiting control group that will not participate in JOBS Program Germany and, thus, not receive effective treatment during the six months of the trial. The unemployed in the waiting control group will complete JOBS Program Germany after the trial has ended.

### Procedure

Due to the country-wide implementation of the JOBS Program Germany in the community-settings, the exact dates of enrollment and trainings will vary across the participating locations. Also, at some locations, more than one JOBS Program Germany will be conducted. However, for any given JOBS Program Germany at a given location, the time schedule is fixed.

Figure 1 shows the time schedule for a typical JOBS Program Germany at a given location. At each of the participating locations and for each JOBS Program Germany there will be an information event for the unemployed. This information event will be scheduled and announced (e.g., via flyer, by agents of the Jobcenters) about 4 to 5 weeks before the JOBS Program Germany starts (−*t*_*1*_). During these information events, two trainers, who will later lead the respective JOBS Program Germany, will explain the intervention and provide participants with a written information sheet that summarizes the objectives, procedure, and contents of the program. Trainers will also address any questions from potential participants. Participation is voluntary and free of charge, and a withdrawal is possible at any time without consequences. At the end of the information events, trainers will obtain written informed consent from the unemployed who are willing to participate.

Following the information event, participants who have given informed consent will be contacted and asked to complete an initial CATI during which participants’ eligibility for the trial is assessed. Participants meet the inclusion criteria if they are between 18 and 65 years old and currently unemployed according to the German Social Code, Book III by the time of the interview. Participants who, by the time of the interview, are full-time students or otherwise inactive on the labour market, and those with insufficient command of the German language to complete the CATI are excluded from the trial.

After assessing the baseline measures, all eligible participants will be randomly assigned to an intervention or waiting control group upon completion of the initial CATI (*t*_*0*_). The allocation (stratified by location) will take place automatically with a 1:1 ratio in an alternating fashion. The first participant who successfully completes the CATI will be allocated to the intervention group; the second participant will be allocated to the waiting control group, and so on. Because allocation is carried out in “real-time”, there is no predetermined list. Hence, whether a participant is allocated to the intervention or control group is not known in advance. Moreover, because at any point in time more than one CATI will be conducted simultaneously, interviewers cannot predict the allocation of a given participant prior to the end of the current interview. The information about the group to which participants will be assigned is only revealed to the interviewers by the time the interview is completed.

Upon completion of the CATI, interviewers will invite participants who are assigned to the intervention group to complete JOBS Program Germany, usually within two weeks. Participants who are assigned to the intervention group might immediately decline participation in the program. The respective persons are then assigned to a separate (waiting control) group and their place in the intervention group is filled with another participant who has not yet been allocated to either group. Any such deviation from the randomly allocated intervention will be recorded in the methods reports and in the dataset. Participants in the waiting control group will be told that JOBS Program Germany will start in 6 months Participants who are randomly allocated to the waiting control group cannot participate in JOBS Program Germany, meaning that it is not possible for participants to self-select into the intervention group.

Participants in the waiting control group are not allowed to join JOBS Program Germany during the 6 months of the trial. However, participants in both the intervention and waiting control group will not actively be discouraged or otherwise prevented from participating in any employment promotion measures of the Federal Employment Agency or any prevention or health promotion measures of their choice other than the JOBS Program Germany. Participation in the intervention is voluntary and may be terminated by the participants at any time.

The post-test interview will take place within 4 weeks after the intervention group has completed JOBS Program Germany (*t*_*1*_). Participants of the intervention group and waiting control group will be asked whether they currently participate or have participated in any measure of the Federal Employment Agency or in any health promotion measure. The intervention group is additionally asked to confirm that they have completed JOBS Program Germany. Primary and secondary outcomes are also assessed.

The final CATI will be conducted 6 months after the intervention group has completed JOBS Program Germany (6-months follow-up, *t*_*2*_). Again, participants in both the intervention and the waiting control group will be asked to report participation in any job-search or health promotion related measure. Also, all outcome measures are assessed. Upon completion of the final CATI, the unemployed in the waiting control group will be invited to complete JOBS Program Germany.

Participants in both the intervention group and the waiting control group will receive a 15 Euro voucher for each completed interview. Participants who, nevertheless, decide to discontinue will be asked for their subjective reasons to do so. We will also collect basic socio-demographic characteristics of all participants during the first interview.

The country-wide recruitment is expected to start in April 2021 and continue until August 2021. We expect that a total of approximately 60 JOBS Program Germany will be conducted between April and September 2021. Given the time schedule with a fixed 6-months follow-up, the trial is expected to end in February 2022.

No adverse effects are expected from completing the JOBS Program Germany. International studies on the JOBS Program found either positive effects ([7], e.g. [10, 11, 13, 14, 17]) or no effects, depending on, e.g., the time span between intervention and follow-up or the specific outcome observed. For instance, Reynolds and colleagues reported several positive effects of the Winning New Jobs Programme (adapted from JOBS Program) implemented in two rural communities in Ireland and Northern Ireland [14]. At the 1-year follow-up, participants of the intervention group were more likely to get reemployed, showed an increased inoculation against setbacks, and showed less economic hardship. However, initially positive effects on job search activities, job-seeking efficacy, and job search motivation did not persist until the 1-year follow-up. Because no adverse effects are expected, the unemployed allocated to waiting control group may join JOBS Program Germany to benefit from any positive effects after the trial has ended. Nevertheless, we will record and publish any negative effects that might occur.

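### Allocation is described as random but specified as alternation within location, so the trial as written is quasi-randomised and its concealment is not assured

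*Protocol article*

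**What the plan says.** Under Methods, Procedure, the protocol article states that "all eligible participants will be randomly assigned to an intervention or waiting control group" once the baseline interview is finished. It then gives the mechanism: "The allocation (stratified by location) will take place automatically with a 1:1 ratio in an alternating fashion". The order is spelled out: "The first participant who successfully completes the CATI will be allocated to the intervention group; the second participant will be allocated to the waiting control" arm, with the pattern continuing from there.

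Three safeguards are offered. Allocation happens in real time without a list drawn up beforehand, from which the article concludes that "whether a participant is allocated to the intervention or control group is not known in advance". It adds that "because at any point in time more than one CATI will be conducted simultaneously, interviewers cannot predict the allocation of a given participant" before the current interview ends. Finally, the assigned group "is only revealed to the interviewers by the time the interview is completed".

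The same section has a replacement rule. Someone who declines an intervention place at once moves to a separate waiting group, and the place passes to a person not yet allocated.

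The Abstract, Trial design and Discussion all call the study a randomised controlled trial. Statistical methods defines intention-to-treat by the randomly allocated group.

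**The concern.** A rule with a fixed starting arm and a fixed order contains no chance. Once the order of completion at a location is given, only one allocation sequence is possible. The claim of random assignment therefore conflicts with the sentences that follow it.

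The concealment argument has the same weakness. Doing without a stored list does not make the next assignment unknown, because the published rule does the work of a list. Simultaneous interviews at other locations do not help either, since each location has its own sequence.

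What is at stake is selection before allocation. Eligibility, including adequate command of German, is assessed in the same interview whose completion triggers the assignment. If the coming arm can be foreseen, judgements on eligibility and on whether an interview counts as complete can depend on it, even unintentionally. The trial is non-blinded, its outcomes are collected by telephone interview, and the target effect is small (d = 0.2, Sample size). Modest selection would therefore matter, and it would enter every primary comparison.

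**Working it through.** The article gives no figure for predictability, so there is nothing to reproduce. The check is first logical, then illustrative.

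**1. Is there a random element?** The rule is: first completer to intervention, then alternate. The arm is a function of completion rank within location: odd rank gives intervention, even rank gives control. A declined place shifts the sequence, but by a stated rule and not by chance. No section of the article adds a random draw.

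**2. What can change a location's next assignment?** Because allocation is stratified by location, only two events can: another interview finishing at that location, or a declined intervention place there. Interviews elsewhere have no effect.

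**3. How often might another same-location interview intervene?** Inputs:
- 1500 participants (Sample size) and about 60 programmes (Procedure), so 1500/60 = 25 per programme.
- Average interview length 30 minutes = 0.5 h (Data collection and management).
- Interviewing 1 to 2 weeks before the programme (note to Table 1). Assumption: 5 to 10 working days of 8 hours, so H = 40 to 80 hours, with interviews spread evenly.

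The chance that none of the other 24 interviews ends during a given one is (1 − 0.5/H)^24:

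| H (hours) | none intervenes | at least one intervenes |
|---|---|---|
| 80 | 0.860 | 0.140 |
| 40 | 0.739 | 0.261 |
| 20 | 0.54 | 0.46 |
| 10 | 0.29 | 0.71 |

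The last two rows show the effect of calls clustering into fewer hours. The result depends strongly on an input that the article does not give.

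**4. How well could the arm be guessed?** Take an interviewer who knows the last same-location assignment and guesses the opposite. With k other same-location interviews open and every finishing order equally likely, the number finishing first is uniform on 0 to k. The guess is right when that number is even:
- k = 0: 100%
- k = 1: 1/2 = 50%
- k = 2: 2/3 = 67%

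For comparison, simple randomisation gives 50%. In a simulation with 25 people per location, permuted blocks of random size (2/4/6 or 4/6) were guessed correctly about 68% to 69% of the time by someone who knew every earlier assignment.

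**The case against.** The strongest defence is that the safeguards are real. Allocation is automatic, and the arm is shown only after the baseline answers are in. Interviewing is centralised with several interviews running at once. An interviewer can exploit the sequence only by knowing the last result at that location, which may belong to a colleague. The article does not say that interviewers see each other's assignments. The replacement rule also shifts the sequence in ways that others cannot anticipate. All of this stands. It is why concealment is best described as not assured, and why 74% to 86% is a ceiling and not an estimate. None of it makes the rule random or supports an absolute statement that prediction is impossible.

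Several stronger readings are tempting but unsupported:
- *Interviewers choose whom to call and when.* The article says only that participants will be contacted. It does not say who sets the order.
- *Starting with intervention overfills that arm or favours it with the most reachable people.* If half of 60 sequences had odd length, the excess would be 60 × 0.5 = 30 people (765 against 735), which is harmless. It also treats programmes as locations, although some locations run more than one programme. The reachability effect amounts to about one rank in 25.
- *The planned tests lose all basis.* They are t-tests and baseline-adjusted regressions, not randomisation tests. What weakens is the guarantee that the groups are comparable.

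It is also fair that small random blocks remain partly guessable. They do, however, avoid the certainty that alternation gives when nothing intervenes.

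**Conclusion.** The point holds as a contradiction in the text. The article calls the assignment random and specifies a deterministic rule, so the trial as written is quasi-randomised. This conclusion needs no assumption.

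The statements on concealment are too absolute. They fail whenever an interviewer knows the last assignment at the location and no other completion or decline there intervenes. In that case the arm is foreseeable before eligibility and completion are settled.

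The frequency cannot be derived from the article. Under the even-spread assumption, 74% to 86% of interviews have no same-location completion in between. This bounds from above how often the arm could be foreseen with certainty, and clustering of calls lowers it. A reader might infer that concealment has failed outright or that the arms will be biased. The article supports neither. It shows that an avoidable route to selection is open.

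The change should be made before enrolment, because allocation cannot be repaired afterwards and every primary comparison rests on it.

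**What to change.** Replace alternation with a computer-generated random sequence stratified by location, for example permuted blocks of randomly varying size. Hold it hidden in the CATI system, and release each assignment only after eligibility and all baseline items are locked. Remove the reasoning that the missing list and the simultaneous interviews make allocation unpredictable. If alternation is kept, describe the trial as quasi-randomised throughout, including in the Abstract, Trial design, Statistical methods and Discussion.

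Real-time allocation, the 1:1 ratio and the sample size stay as they are. The cost is minor CATI programming and a revised paragraph, plus possible small imbalances within a location when a block is left incomplete (at most 3 people if the largest block is 6). Larger blocks are harder to guess but allow more imbalance.

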### Statistical methods

Statistical methods will include t-tests (or equivalent tests for proportions) as well as linear and (binary) logistic regression models. We will compare primary and secondary outcomes between the intervention and waiting control groups.

Reintegration into the labor market (employed vs. unemployed) and the type of contract (temporary vs. permanent) will be assessed using t-tests (or equivalent test of proportions) and logistic regression models. In all analyses, we will treat Likert-Type items as continuous variables. For life-satisfaction, depressive symptoms, and psychological distress, we will first construct (additive) indices. We will then test mean differences in the respective indices between intervention and waiting control groups using t-tests. In multivariate analyses, we will use linear regression models to adjust for baseline-measures of the respective outcomes. Additional models will also adjust for socio-demographic characteristics and indicators of labor market biography, such as the duration of unemployment. We proceed in a similar fashion to analyze self-esteem, self-efficacy and our secondary outcomes job satisfaction and job-search intensity.

To test for potential effect modifications, we include interaction terms between our treatment-indicator and the respective moderators (job-search intensity, duration of unemployment) in the respective regression models.

All multivariate analyses will include controls for socio-demographic variables and (un-)employment history. We will repeat our main analyses stratified by gender. All analyses will be carried out according to the  “intention-to-treat” principle. Participants will be treated as belonging to the group to which they were originally (randomly) allocated. We tolerate low proportions of missing values of up to 5%, and perform listwise-deletion (complete-case analyses). If the proportion of missing values exceeds the predefined threshold of 5%, we will treat missing values by means of multiple imputation [31–33].

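### Intervention-arm decliners are moved out and replaced after the arm is disclosed; unless they are followed and analysed as intervention, which the plan does not say, the comparison is selected on one side

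*Protocol article*

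**What the plan says.** All of the following is in the protocol article.

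- **Allocation (Procedure).** "The allocation (stratified by location) will take place automatically with a 1:1 ratio in an alternating fashion". The arm is revealed when the baseline telephone interview is complete.
- **Refusal (Procedure).** "Participants who are assigned to the intervention group might immediately decline participation in the program". On what happens to decliners, the article states: "The respective persons are then assigned to a separate (waiting control) group". On the vacancy that this leaves, it adds: "their place in the intervention group is filled with another participant who has not yet been allocated to either group".
- **Recording (Procedure).** On documentation, it promises: "Any such deviation from the randomly allocated intervention will be recorded in the methods reports and in the dataset".
- **Stated safeguard (Procedure).** Controls cannot enter the programme during the trial, so "it is not possible for participants to self-select into the intervention group". Selection out of the intervention arm is not addressed.
- **Analysis (Statistical methods).** All analyses follow intention-to-treat: "Participants will be treated as belonging to the group to which they were originally (randomly) allocated".
- **Numbers (Sample size, Table 1).** Two groups of 750 at allocation, 600 at the post-test and 450 at six months.

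The article does not say whether the separate group is a third group or part of the control arm, whether its members are interviewed at t1 and t2, or in which arm they are analysed. The interview schedule under Procedure mentions only the intervention group and the waiting control group.

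**The concern.** The rule acts after disclosure and on one arm only. An intervention participant is offered a course place and can refuse it. A control participant is told that the course starts in six months and has nothing to refuse at that moment. Because a replacement who refuses would be replaced in turn, the filled intervention places hold acceptors only, while the control arm holds acceptors and would-be decliners together.

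Willingness to attend a job-search course once a place is offered is plausibly related to job prospects, motivation and depressive symptoms, which are close to the primary outcomes. If the filled groups are compared, part of any difference reflects who accepted. The sign cannot be predicted: decliners may be people who expect a job soon, or people who are discouraged. Adjustment for baseline measures would not reliably remove it.

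There is also a question of consistency. Moving people to another group and analysing them as originally allocated can both hold only if decliners stay under follow-up and count as intervention. The article does not state that.

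**Working it through.** **1. The plan's own sample size.** Inputs from Sample size: effect 0.2 SD, two-sided alpha 0.05, power 85%.

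n per group = 2 × (1.960 + 1.036)² / 0.2² ≈ 449, against 450 stated. Power at 450 is 85.1%. For re-employment of 30% against 40%, 407 per group are needed (427 with continuity correction), and 450 gives 88.3%. The 450 is sound, and 900 / 0.60 = 1500 matches Table 1. (The text calls 60% the dropout rate, whereas Table 1 retains 60%. That is a separate matter; Table 1 is used here.)

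**2. Bias if the filled groups are analysed.** Let d be the share declining and g the mean outcome of acceptors minus that of decliners. Neither is in the document, so all values are assumptions. The true effect is set to zero, with 450 filled intervention places and 450 ordinary controls. The intervention arm is all acceptors.

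- *(a) Decliners left out.* The control arm has a decliner share of d, so bias = d × g.
- *(b) Decliners counted as controls.* Filling 450 places produces 450·d/(1 − d) decliners. The decliner share in the enlarged control group is [450d + 450d/(1 − d)] / [450 + 450d/(1 − d)] = d(2 − d), so bias = d(2 − d) × g.

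Example for re-employment, d = 20%, g = 15 points:
- (a) 0.20 × 15 = 3.0 points.
- (b) 0.20 × 1.80 × 15 = 0.36 × 15 = 5.4 points.

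The type I error is the two-sided rejection rate, by normal approximation, when the only difference is this bias.

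| Outcome | d | g | (a) bias | (a) type I error | (b) bias | (b) type I error |
|---|---|---|---|---|---|---|
| Scale | 5% | 0.2 SD | 0.010 SD | 5.3% | 0.020 SD | 6.0% |
| Scale | 10% | 0.3 SD | 0.030 SD | 7.3% | 0.057 SD | 14.2% |
| Scale | 20% | 0.3 SD | 0.060 SD | 14.7% | 0.108 SD | 40% |
| Re-employment | 10% | 15 points | 1.5 points | 7.8% | 2.9 points | 16% |
| Re-employment | 20% | 15 points | 3.0 points | 16% | 5.4 points | 46% |

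A negative gap reverses the sign of the bias and leaves its size the same.

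**3. Allocation ratio if decliners are kept but places are still refilled.** Filling 750 places when 10% of those offered decline takes 750 / 0.90 ≈ 833 people assigned to the intervention, against 750 controls. At 20% it is 750 / 0.80 ≈ 938. The arms then no longer match 1:1 or Table 1.

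**4. Power when decliners are kept and not replaced.** Assume that decliners gain nothing, so the effect becomes 0.2 × (1 − d). Recruits = 2 × n / 0.60.

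| d | Effect | Power at 450 per arm | n per arm for 85% | Recruits |
|---|---|---|---|---|
| 5% | 0.19 | 81.3% | 498 | 1660 |
| 10% | 0.18 | 77.0% | 555 | 1850 |
| 20% | 0.16 | 67.0% | 702 | 2340 |

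For re-employment (30% against 30% plus 10 points × (1 − d)), power at 450 is 85.0%, 81.2% and 71.7%.

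**The case against.** The strongest reply is that Procedure governs who gets a course place and Statistical methods governs who is analysed where. The analysis rule refers to original allocation, which matters only if some people change group, and deviations are recorded in the dataset. Decliners could therefore be restored to the intervention arm. This stands: a reader might infer that the plan flatly contradicts intention-to-treat, and the text does not go that far. What remains is that the article never says that decliners are analysed as intervention, and its interview schedule does not clearly cover them. A recorded deviation without follow-up gives no outcome to analyse.

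A reader might also infer that the trial compares willing people with everyone. It does not. Both arms consented after an information event, for a course with a fixed schedule. Only refusals after that consent are at issue.

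Nor does the text suggest that replacements are chosen for their prognosis. The vacancy arises from another person's refusal, and the natural reading is that the next person to complete the interview fills it. If decliners are kept, replacement mainly alters the ratio and the alternating sequence; a large bias of its own is not shown.

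Table 1 lists attrition assumptions, so the lack of a row for decliners is not an error. The sentence on self-selection into the intervention is true of controls as written; it simply does not cover selection out.

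**Conclusion.** The point holds in a conditional form. If the groups that result from reassignment and replacement are compared, the intervention arm is selected for acceptance after disclosure and the comparison is biased. The article does not exclude that comparison, because it does not say where decliners are followed or analysed. If they are analysed as intervention, their selection is removed, but refilling still disturbs the sequence and the 1:1 ratio.

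The size is unknown because neither the decline share nor the outcome gap is given. It runs from negligible (5% decline, 0.2 SD gap) to a substantial part of the 10-point target difference in re-employment (20% decline, 15-point gap). A reader might infer that a large distortion is certain; these are scenarios and do not support that. The rule is still worth changing before recruitment, since it touches every primary outcome and modelling cannot reliably repair it afterwards.

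**What to change.** 1. Delete the reassignment and replacement rule. Keep each decliner in the intervention arm, interview them at t1 and t2, and say in Statistical methods that they are analysed there.
2. Allocate the next participant by the ordinary allocation rule, whatever earlier participants decided.
3. In the telephone interview, confirm availability and willingness for the fixed course dates before allocation is triggered. Refusals then fall mostly before allocation, where they affect both arms alike.
4. Flag anyone already placed as a replacement and run a sensitivity analysis without them.
5. State the power with an allowance for decliners, for example the 5%, 10% and 20% rows above.

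The change needs a revised interview script and a few protocol sentences. Its real costs are somewhat smaller course groups and a diluted intention-to-treat effect: at 450 per arm, power for 0.2 SD falls to about 81%, 77% or 67%. Restoring 85% would take 1660, 1850 or 2340 recruits instead of 1500. Step 3 is what keeps this cost near the low end.
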